### The LightCafé Approach

In the *LightCafé* and *LightCafé* + conditions, BLT is administered in the *LightCafé*. This café-like environment is intentionally designed to provide a comfortable, informal, and welcoming atmosphere, in stark contrast to traditional clinical environments. The interior design of *LightCafé* emphasizes restorative elements, with soothing colors, comfortable seating, and natural light exposure, while the layout encourages social interaction among patients. Various decor elements, such as plants and artwork, contribute to a warm and inviting environment that enhances overall well-being. Figure 1 provides a visual representation of *LightCafé*.

**Fig. 1 Fig1:**
[figure not shown]
The LightCafé is a café-style space where each participant receives BLT against a backdrop of restorative design elements (e.g., ample natural light, greenery, artwork, and clustered seating). Sessions include 5–10 min of one-on-one lifestyle coaching with professional and take-home workbooks for self-guided sleep-, exercise-, and nutrition-support. All trial participants in the LightCafé and LightCafé+ arms are treated in this setting. Photo: Boschdijk location, GGzE Eindhoven en de Kempen, Netherlands

Each BLT session in the *LightCafé* includes 5–10-min consultations with a professional nurse or psychologist, during which participants discuss various aspects of their lifestyle, such as sleep hygiene, exercise, nutrition, daily routines, social interaction, and overall healthy living. These brief consultations are integrated into the light therapy sessions to provide personalized guidance and support. Additionally, participants are provided with workbooks designed for independent use, enabling them to actively work on and improve their lifestyle habits outside of the sessions. The ultimate goal of the *LightCafé* approach is to foster a stable rest-activity pattern, promote a more active lifestyle, ensure a fulfilling daily routine, and encourage social interaction, all within a treatment environment that enhances the overall treatment experience.

### Personalized chronotherapeutic strategies

In the *LightCafé* + arm, BLT timing is personalized, and participants wear BBG according to their individual sleep–wake rhythms. These adjustments aim to promote sleep regularity and synchronize sleep phase with the endogenous biological night. Before commencing treatment, each participant’s current sleep onset time (CSO) is established based on their baseline sleep data obtained from the Consensus Sleep Diary (CSD; [60]. Following this, a target sleep onset time (TSO) is collaboratively determined through a phone call with a member of the study team. During this conversation, the participant’s daily routine, social and work obligations, and personal preferences for sleep onset and offset are discussed. The aim is to establish a sleep schedule that accommodates approximately 7–8 h of nightly sleep and fits well within the participant’s everyday life.

Based on the relation between CSO and TSO, one of the following timing strategies is employed:*Stabilize*: When CSO is within 30 min of TSO, the aim is to not shift sleep timing and the circadian clock. Morning BLT is administered approximately 11 h after TSO, and participants wear BBG during the last hour before TSO.*Advance*: When CSO occurs more than 30 min later than TSO, the aim is to advance the sleep timing and the biological clock by exposing patients to BLT earlier in the morning (around 8–9 h after CSO) and having them wear BBG during the last 2 h before CSO.*Delay*: In cases where CSO is more than 30 min earlier than TSO, a delay in sleep–wake cycles and the biological clock is the goal. Morning BLT is administered later in the morning (around 11 h after CSO), and BBG are worn in the morning, during the first 2 h after awakening.

The chronobiological strategy is selected and implemented on a weekly basis, based on a reassessment of the CSO, using CSD entries from that week, and the TSO, determined via phone contact. Treatment times will always remain within the 7:30 AM to 10:30 AM window. This time frame was chosen because morning light has been shown to be most effective in reducing depressive symptoms [7]. While some individuals may theoretically benefit from alternative timings, individual adjustments are limited by the practical constraints of the clinical setting. If the prescribed strategy suggests a time outside this window, the closest suitable time within the range is selected.

### Criteria for discontinuing or modifying allocated interventions {11b}

Participants can withdraw from the study at any time without providing a specific reason. BLT is discontinued upon the patient achieving remission or exhibiting mania symptoms as per the YMRS or clinical assessment. Furthermore, treatment discontinuation can be initiated by clinical staff when they consider it to be in the best interest of the patient.

### Strategies to improve adherence to interventions {11c}

Treatment adherence is assessed using two complementary methods: EMA and personal light exposure sensors. Each day, participants receive a smartphone questionnaire asking whether they adhered to the light therapy protocol. If not, they are prompted to indicate the reason for non-compliance. In parallel, participants wear personal light exposure sensors throughout the study period to objectively record light exposure and verify whether the prescribed timing and dosage were followed.

To support protocol adherence and increase participant engagement, a feedback session is scheduled after the post-treatment assessment. During this session, participants receive personalized feedback based on their individual data (e.g., daily affect changes, and actigraphy reports) collected during the intervention.

### Relevant concomitant care permitted or prohibited during the trial {11d}

Participants are allowed to continue existing antidepressant treatments alongside BLT, provided these therapies—pharmacological or non-pharmacological—were initiated at least 2 months prior to study entry. This includes antidepressant medications, psychotherapy, EMDR, or other interventions aimed at reducing depressive symptoms. While the initiation of new treatments or dosage adjustments during the study period is discouraged, they are not prohibited. Any such changes will be carefully documented and accounted for in the statistical analysis to control for potential confounding effects.

### Provisions for post-trial care {30}

In the event of a successful treatment, the opportunity for another round of BLT becomes available 3 months after the last treatment session, provided there are no clinical contraindications, and the final follow-up of the study has been completed. If the treatment is considered unsuccessful, official communication will be sent to the referring healthcare provider, and the responsibility for further treatment will rest with them.

Participants in this study are not provided with research subject insurance coverage, as BLT is a non-invasive treatment associated with a low likelihood of mild and short-term side effects.

### Outcomes {12}

#### Primary study outcome—clinical improvement in depressive symptoms

The primary outcome of this study is the clinical improvement in depressive symptoms assessed with the Montgomery Åsberg Depression Rating Scale (MADRS; [78]) from baseline to post-treatment. Independent raters, unaware of participants’ treatment conditions and assessment points, will conduct MADRS evaluations. Other key metrics based on the MADRS include remission (participants with post-treatment scores of 10 or lower [79]) and response rates (participants with 50% reduction in depressive symptoms from baseline to post-treatment assessment).

### Secondary study outcomes

We assess a range of secondary outcomes, categorized as mood-related and functional outcomes, sleep-related outcomes, circadian parameters, brain imaging parameters, and light-related parameters.

## Mood-related and functional outcomes

Complementary to the clinician-rated depressive symptoms, self-reported depressive symptoms will be evaluated using the QIDS-SR, administered weekly from baseline to post-treatment, as well as at the 10-week and 4-month follow-ups. In addition to tracking self-reported depression scores over time, we will utilize QIDS-SR data to assess self-rated remission rates, self-rated response rates, time to remission, and relapse rates.

Momentary affect measures are evaluated using EMA to assess mood throughout the day. From the baseline week through 1 week after treatment, participants receive eight daily smartphone alerts containing items from the Positive and Negative Affect Scale [80] the Activation-Deactivation Adjective Check List [81] and additional items adapted specifically for this EMA. Momentary Positive Affect (PA) is assessed using the average score of three items in the EMA: “I feel cheerful,” “I feel content,” and “I generally feel well,” each rated on a 7-point scale from 1 (*not at all*) to 7 (*very*). Momentary Negative Affect (NA) is evaluated using the average of six items: “I feel irritated,” “I feel insecure,” “I feel lonely,” “I feel anxious,” “I feel down,” and “I feel guilty,” rated similarly. Diurnal mood variations will be assessed by comparing momentary affect states in the morning with momentary affect in the afternoon and evening.

Functional outcomes will be evaluated using the Short Form Health Survey (SF-12; [82]), the Mental Health Quality of Life Questionnaire (MHQoL; [83]), at baseline, post-treatment, and during follow-up, providing us with parameters for overall functioning and quality of life, respectively.

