### Follow-up phase

After the treatment has been completed, EMA, actigraphy, and light logger usage are extended for an additional week and are discontinued on the Sunday at the end of this additional week. The post-treatment DLMO assessment (M3) and MRI scan (MRI-2) also occur within this first week after BLT.

Following these assessments, a post-treatment evaluation (PT1) is scheduled 4 weeks after the start of treatment, which includes a series of online questionnaires and an online MADRS assessment. During this meeting, participants receive general insights into their EMA data. The online follow-up questionnaires (F1) are sent 10 weeks after the start of treatment, with the second set of follow-up questionnaires (F2) distributed 4 months after the start of treatment, after which study participation is discontinued.

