			***Treatment***			
	*Intake*	*B1*	*Evaluation*	*PT1*	*F1*	*F2*
**Mini International Neuropsychiatric Interview (M.I.N.I.)** [69] ***(clinical diagnosis of psychiatric disorders)***	X					
**Sociodemographics**	X					
**Current Medications and Therapies **	X			X	X	X
**Quick Inventory of Depressive Symptomatology Self-Report (QIDS-SR)** [70] ***(Self-reported Severity of Depressive Symptoms)***	X	X	X	X	X	X
**Montgomery-Åsberg Depression Rating Scale (MADRS)** [78] ***(Clinician-rated Severity of Depressive Symptoms)***		X		X		
**Morningness-Eveningness Questionnaire (MEQ)** [86] ***(Chronotype – Morningness/Eveningness preference)***	X				X	
**Ultra Short Munich Chronotype Questionnaire (µMCTQ)** [87] ***(Chronotype – Sleep Timing)***	X	X		X	X	X
**Pittsburgh Sleep Quality Index (PSQI)** [84] ***(Subjective Sleep Quality)***		X		X	X	X
**Insomnia Severity Index (ISI)** [85] ***(Severity of Insomnia Symptoms)***		X		X	X	X
**Short Form Health Survey - 12 items (SF-12)** [82] ***(Health-related functional outcomes)***		X		X	X	X
**Mental Health Quality of Life (MHQoL)** [83] (***Quality of Life related to Mental Health***)		X		X	X	X
**Credibility/Expectancy Questionnaire (CEQ)** [71] ***(Treatment credibility and participant expectations)***		X				
**Adverse Event Scale** ***(Occurrence and severity of adverse events)***			X			
**Young Mania Rating Scale (YMRS)** [96] ***(Symptoms of (hypo)mania)***			X			

This table gives an overview of the questionnaires utilized at various assessment points in the Baseline, Treatment, and Follow-up. Each questionnaire’s purpose is indicated alongside the time points at which it was administered indicated with an X. No questionnaires are administered during melatonin assessments (M1, M2, M3) or MRI sessions (MRI-1, MRI-2)

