### Secondary Study Outcomes

#### Subjective Assessment of Depressive Symptoms, Relapse Rates and Functional Outcomes

Multilevel mixed-effects models will be constructed to assess depressive symptom improvement, measured weekly during therapy and at follow-up assessments using the QIDS-SR scores as the dependent variable. Fixed effects will include timepoint as an categorical variable (baseline, 1 week, 2 weeks, 3 weeks, 4 weeks, 10 weeks, and 4 months), and the interaction between timepoint and treatment condition (*Light@Home*,* LightCafé*, and *LightCafé* +). Random intercepts and slopes will be included for participants and study centers, as well as random slopes for time within participants, based on model fit criteria. Confounding variables (age, sex, clinical diagnosis, and credibility/expectancy of treatment) will also be evaluated and included as necessary. A variable will be added to account for treatment duration (1 week, 2 weeks, 3 weeks). Similar models will be considered for analyses of relapse rates, functional outcome, and Quality of Life with inclusion of the respective timepoints as fixed effects (see Table 1).

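### Relapse is taken from QIDS-SR readings at week 10 and month 4, so a relapse that is treated and recovers between readings is counted as no relapse, although treatment changes are recorded

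*Protocol article*

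**What the plan says.** **Source of the outcome.** Under Mood-related and functional outcomes: "we will utilize QIDS-SR data to assess self-rated remission rates, self-rated response rates, time to remission, and relapse rates". No other data source is named for relapse.

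**Reading times.** The QIDS-SR is taken weekly up to post-treatment, "as well as at the 10-week and 4-month follow-ups". Under Follow-up phase, "a post-treatment evaluation (PT1) is scheduled 4 weeks after the start of treatment" and "The online follow-up questionnaires (F1) are sent 10 weeks after the start of treatment". The last set (F2) follows 4 months after the start of treatment. The instrument description under item {18a} gives a 7-day recall.

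**New treatment.** Item {11d}: "While the initiation of new treatments or dosage adjustments during the study period is discouraged, they are not prohibited". The same section promises that changes will be documented and handled in the analysis as potential confounding. Table 1 has a row "Current Medications and Therapies", marked at Intake, PT1, F1 and F2.

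**Analysis.** In the section on QIDS-SR, relapse and functional outcomes: "Similar models will be considered for analyses of relapse rates, functional outcome, and Quality of Life". The model they are to resemble lists age, sex, diagnosis, credibility/expectancy and treatment duration. Treatment begun after remission is not listed. The one concrete plan for medication, type and dose as time-varying covariates under item {20b}, is for the primary outcome models.

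**The concern.** Objectives {7} asks whether the café setting and personalised timing prolong the antidepressant effect as well as enlarge it. Relapse bears directly on that question.

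Up to week 4 the weekly QIDS-SR gives little room for an unseen relapse. After week 4 there are two readings in about three months. In that period a patient who feels worse may obtain treatment, recover, and score in the remitted range at the next reading. The QIDS-SR then shows no relapse, although the patient relapsed and needed treatment. The evidence of that event would sit in the therapy form collected at the same visit, which the relapse outcome does not use.

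Relapse would then be under-counted overall. If treatment-seeking or speed of recovery differed between arms, part of any difference in relapse would reflect that and not durability of effect.

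**Working it through.** The protocol states no relapse rate and no power for relapse, so there is no figure of its own to reproduce. The check uses its reading times.

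**1. Follow-up seen by the QIDS-SR**
- PT1 is at day 28 (week 4) and F1 at day 70 (week 10). F2 is at day 112 to 122 (4 months as 16 weeks or as calendar months).
- Days from PT1 to F2: 112 − 28 = 84, or 122 − 28 = 94.
- Two 7-day recall windows cover 14 days. The uncovered share is 1 − 14/84 = 83% to 1 − 14/94 = 85%.

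This is not the share of relapses missed, because an episode lasting weeks can reach into a reading.

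**2. Share of treated relapses missed**

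Assumptions: onset is uniform between PT1 and F2; the score falls back below the cut-off D days after onset and stays there. D includes the time to notice the relapse, obtain care and respond. The two gaps are 42 days (day 28 to 70) and G = 42 or 52 days (day 70 to F2). Let w = 7 if any overlap with the recall window counts as detected, and w = 0 if symptoms must be present on the reading day.

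Missed share = [max(0, 42 − w − D) + max(0, G − w − D)] / (42 + G)

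| D (assumed) | lowest (G = 42, w = 7) | highest (G = 52, w = 0) |
|---|---|---|
| 14 days | (21 + 21)/84 = 50% | (28 + 38)/94 = 70% |
| 21 days | (14 + 14)/84 = 33% | (21 + 31)/94 = 55% |
| 28 days | (7 + 7)/84 = 17% | (14 + 24)/94 = 40% |
| 42 days | 0/84 = 0% | (0 + 10)/94 = 11% |
| 56 days | 0% | 0% |

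The documents do not give D. Their background sections point both ways: antidepressants often need weeks for full effect, while relief under light therapy typically comes within 1 to 2 weeks.

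**3. Effect on an arm comparison (assumed inputs, mechanism only)**
- True relapse 30% in two arms, with 10% of relapses missed in one and 30% in the other: 0.30 × 0.90 = 27% against 0.30 × 0.70 = 21%. A 6-point difference appears where none exists. Swapping the arms reverses its sign.
- With 20% missed in both: 0.30 × 0.80 = 24% in each arm. There is no false difference, but both rates are too low.

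**4. Whether the stated adjustment repairs it**

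Treatment started because of a relapse comes after the relapse and is caused by it. Entering it as a covariate leaves the patient coded as no relapse at both readings. It also conditions the arm comparison on something that happened after randomisation and may depend on arm. The covariates under item {20b} do not reach this outcome, because the primary outcome ends at PT1, before the gap opens.

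**The case against.** **Detail of this kind belongs in the analysis plan.** The article calls its methods an initial framework and says only that similar models will be considered for relapse. This stands for the cut-off and the prior-remission rule, and their absence is not the point here. The data source for relapse is stated, however, and that is what is challenged.

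**Reading the QIDS-SR regardless of later treatment fits intention-to-treat.** It does, and it suits the analysis of QIDS-SR scores over time. For relapse it answers a narrower question: whether the patient was depressed in either of two particular weeks.

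**The gap may be small.** If recovery takes six weeks or more, little or nothing is lost. This stands, and it limits the size.

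**A composite counts treatment-seeking as relapse.** Some changes will have other reasons. This stands as a cost, and it is why both definitions should be reported.

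Four stronger readings are tempting but not supported:
- *That patients may start treatment freely.* Item {11d} discourages it and has changes documented.
- *That a missed relapse is scored as sustained benefit.* No such endpoint is defined; the patient is simply counted as not relapsed.
- *That the error favours the café arms.* Sessions end by week 3 at the latest, and no arm-specific professional contact is described afterwards. Treatment-seeking in follow-up could differ in either direction or not at all.
- *That the post-trial care section widens the gap.* Its provision that "official communication will be sent to the referring healthcare provider, and the responsibility for further treatment will rest with them" applies when treatment is judged unsuccessful, so it mostly concerns patients not at risk of relapse after remission. The further round of light therapy it offers comes only after final follow-up.

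**Conclusion.** The point holds for a secondary outcome. As stated, relapse rests on QIDS-SR data with two readings after week 4. Treatment started for a relapse is permitted and recorded but does not count, so a relapse that is treated and recovers between readings is lost. The promised confounder adjustment cannot recover it.

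Among such treated relapses, the missed share is about 17-40% if recovery takes 4 weeks and 0-11% if it takes 6 weeks. This assumes uniform onset, lasting recovery and month 4 at day 112 to 122. The share of all relapses that is missed cannot be derived, because the documents give neither a relapse rate nor a rate of new treatment. The direction of any bias between arms is unknown. The primary MADRS comparison is unaffected, and the QIDS-SR score models through month 4 still bear on durability. The change is worth making because it is cheap and the form already exists.

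**What to change.** - Among participants who reached remission, count as relapse either a QIDS-SR back in the depressed range, with the cut-off stated, or a start or increase of antidepressant treatment for depressive symptoms between PT1, F1 and F2, taken from the form "Current Medications and Therapies".
- Confirm that this form captures the reason for a change and its approximate start date. If it does not, add those two items while recruitment continues.
- Report the QIDS-SR-only definition alongside as a sensitivity analysis.
- Do not adjust the relapse model for treatment started after remission.

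The cost is analysis-plan wording and at most two form items; no rule on concomitant treatment changes. The downside is that some treatment changes made for other reasons may be counted. The condition that the change be for depressive symptoms limits this, and the sensitivity analysis shows how far the two definitions differ. A relapse that resolves between readings without any treatment change would still be missed.

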## Sleep-Related Outcomes

Subjective sleep metrics are collected using a short version of the CSD which is administered daily during the baseline, treatment, and first follow-up week through the use of EMA (morning prompt). Key metrics derived from this diary include sleep duration, sleep onset, sleep onset latency, sleep offset, midsleep timing, wake after sleep onset, and sleep quality. Concurrently, objective sleep metrics are obtained from actigraphy data collected using the MotionWatch8 (CamNtech, Cambridge, UK) during the baseline, treatment, and first week post-treatment. Objective sleep parameters mirror those of the subjective measures and include sleep duration, sleep onset, sleep onset latency, sleep offset, midsleep timing, wake after sleep onset, sleep fragmentation, and sleep efficiency.

Momentary Energy Levels are evaluated using the average score on the EMA items “I feel energetic,” “I feel active,” and “I feel lively,” and the additional question “how alert or sleepy do I feel right now?” rated from 1 (*extremely sleepy*) to 9 (*extremely alert*). Additionally, subjective sleep quality and insomnia severity are assessed using the Pittsburgh Sleep Quality Index (PSQI; [84]) and the Insomnia Severity Index (ISI; [85]), administered at baseline, post-treatment, and during the 10-week and 4-month follow-ups.

## Circadian rhythm parameters

Dim Light Melatonin Onset (DLMO) is evaluated at baseline and post-treatment as the gold standard for determining circadian phase. This assessment involves collecting eight saliva samples around habitual sleep onset. DLMO was defined as the time when melatonin concentrations exceeded the 3 pg/mL threshold upon linear interpolation of subsequent melatonin values and continued to rise. Additionally, we assess the phase angle difference between DLMO and sleep onset (based on actigraphy), a crucial metric for evaluating circadian misalignment. We also analyze actigraphy-derived metrics, including the least active 5-h period (L5), the most active 10-h period (M10), and the difference in activity between L5 and M10, which serves as a proxy for amplitude. Other metrics derived from actigraphy include rest-activity periodicity, inter-daily stability, and intra-daily variability. Furthermore, we evaluate chronotype using the Morningness-Eveningness Questionnaire (MEQ; [86]) and the ultra-short Munich Chronotype Questionnaire (µMCTQ; [87]), both administered at baseline and post-treatment.

